**Methods:**

This is an observational category matching case-control study. We aim to recruit 75 frail older adults and 75 matched non-frail older participants (1:1), to be assigned respectively to the case and control groups. All subjects will undergo sEMG of the lower limb muscles during a 10-meter walk test and will be assessed for gait and balance. The primary outcome will be the difference in sEMG parameters between the two groups, including root mean square (RMS), integrated electromyography (IEMG), averaged electromyography (AEMG), mean power frequency (MPF), and median frequency (MF), as well as those computed from these metrics, including symmetry index (SI), muscle activation sequences, and muscle contribution rates. Secondary outcomes will encompass the time taken to complete the 10-meter walk test and assessments of gait and balance. Furthermore, the relationship between electromyographic parameters and the state of frailty will be evaluated, and the predictive capability of these sEMG parameters for identifying frailty will be explored.

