### Primary and secondary objectives

The primary objective of this study is to compare the surface electromyography (sEMG) signal parameters of the rectus femoris, semitendinosus, tibialis anterior, and medial head of the gastrocnemius muscles in both lower extremities during a 10-meter walk test between frail and non-frail older adults in order to characterize changes in lower extremity sEMG signals in frail older adults.

Secondary objectives are to explore the correlations between EMG parameters and frailty states and to assess the predictive validity and diagnostic value of EMG parameters for frailty states.

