### Selection criteria

#### Inclusion criteria.

(1)Case group1)Older individuals evaluated as frail using the Fried’s frailty phenotype [24], which includes five criteria: (i) Unintentional weight loss: a loss of more than 4.5 kg or more than 5% of body weight over the past year, excluding dieting and exercising. (ii) Slowed walking speed: time taken to walk 4.57 meters, assessed in conjunction with height and gender. (iii) Reduced grip strength: older adults are instructed to measure grip strength twice with their usual hand, and the average of these two measurements is evaluated against gender and body mass index (BMI). (iv) Decreased physical activity: measured using the Minnesota Leisure Time Activity questionnaire, with activity levels less than 383 kcal/week for men (approximately 2.5 hours of walking) and less than 270 kcal/week for women (about 2 hours of walking) indicating a reduction. (v) Self-reported fatigue: assessed using two questions from the Center for Epidemiological Studies-Depression (CES-D). Question 1: ‘I felt that everything I did was an effort during the past week.’ Question 2: ‘I could not get “going” during the past week.’ Scoring for questions 1 and 2 assigns 0 points for less than 1 day, 1 point for 1–2 days, 2 points for 3–4 days, and 3 points for more than 4 days, with a score of 2–3 points on any question indicating significant fatigue. One point is awarded for each criterion met, with a higher score indicating greater frailty. Scores of 3 or more indicate frailty, scores of 1–2 indicate pre-frailty, and a score of 0 indicates no frailty. 2) Age 60 years old and above. 3) Those who can walk independently without assistive devices. 4) Those who possess normal reading, understanding, and expressive abilities to engage in relevant assessments and tests. 5) Those who voluntarily participate in the study and sign the informed consent form.(2)Control group.

The control group will include older adults without frailty, with all other inclusion criteria identical to those of the case group.

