### Sample size calculation

The sample size calculation was performed using G*Power 3.1.9.7, based on an effect size of 0.433 derived from pilot study data. With a power of 80% and an alpha level of 0.05, the required sample size was calculated to be 67 subjects per group. Anticipating a 10% attrition rate, the sample size was adjusted to 75 subjects per group, resulting in a total of 150 subjects to ensure adequate power for detecting significant differences.

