### Statistical analysis

Statistical analysis will be conducted using SPSS 24.0 software, with graphical representations generated through Graph Pad Prism 8. Measurement data will be analyzed by the Kolmogorov-Smirnov test (K-S test), expressed as mean ± standard deviation (x̅ ± s) if they adhere to a normal distribution, with comparisons between groups made using the two independent samples t-test. For non-normally distributed data, results will be described using the median (interquartile range) [M(IQR)], and comparisons between groups will be conducted using the Mann-Whitney U test. Count data will be expressed as frequency (n) and constitutive ratio (%), with comparisons between groups performed using the χ^2^ test or Fisher’s exact test, and rank data comparisons utilizing the Wilcoxon rank-sum test. Effect sizes will be calculated using Cohen’s d value, and the significance level will be set at a two-sided *P *< 0.05.

The intraclass correlation coefficient (ICC) analysis, specifically the ICC(3,k) model, will be used to quantify the consistency and reproducibility of measurements. To assess the reliability of single measurements, the standard error of measurement (SEM) will be calculated using the formula SEM = SD/$\sqrt{n}$, where n represents the number of measurements per participant (i.e., 3). Additionally, the minimum detectable difference (MDD) will be calculated using the formula MDD = SEM × 1.96×$\sqrt{2}$ to determine whether observed differences exceed those expected from measurement error alone, at the 95% confidence level.

Associations between sEMG parameters and frailty status will initially be assessed using Pearson correlation analysis for normally distributed data or Spearman rank correlation analysis for non-normally distributed data. Subsequently, EMG parameters significantly associated with frailty status will be included in binary logistic regression models to further assess their predictive ability for frailty status, controlling for potential confounders such as age and gender. Finally, EMG parameters that prove significant in the logistic regression analysis will be evaluated for their sensitivity, specificity, and cutoff values for diagnosing frailty using receiver operating characteristic (ROC) curves.

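### The sEMG predictors of frailty are chosen, refitted and given ROC cut-offs on the same 75 + 75 people with no optimism correction stated, so the reported accuracy will be biased upward

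*Protocol article*

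**What the plan says.** The Statistical analysis section of the protocol article sets a chain of three steps:

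1. Each sEMG parameter is correlated with frailty status (Pearson or Spearman).
2. "EMG parameters significantly associated with frailty status will be included in binary logistic regression models to further assess their predictive ability for frailty status", with adjustment for confounders such as age and gender.
3. "EMG parameters that prove significant in the logistic regression analysis will be evaluated for their sensitivity, specificity, and cutoff values" by ROC curve.

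The only significance level given is two-sided 0.05. The chain serves a stated secondary objective, "to assess the predictive validity and diagnostic value of EMG parameters for frailty states". The article describes one convenience sample of 75 frail and 75 non-frail adults. It mentions no hold-out sample, resampling, shrinkage or multiplicity adjustment for this part. The follow-up work named in the Discussion tracks participants' progression and is not a validation of cut-offs.

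**The concern.** A parameter reaches the ROC step only because it separated the two groups in these particular people. Its AUC and best cut-off are then read from the same people. The selection has already removed parameters that looked weak by chance and kept those that looked strong by chance, so AUC, sensitivity and specificity are biased upward and the cut-off is tuned to this sample. The bias grows with the number of candidates, and here that number is large relative to the number of cases.

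At stake is the diagnostic objective. The Discussion foresees screening indicators for early detection, and a published cut-off may be taken up by others at face value.

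**Working it through.** **The plan's own figures.** The article gives no target AUC and no sample size for prediction. Its size calculation is for a group difference: "With a power of 80% and an alpha level of 0.05, the required sample size was calculated to be 67 subjects per group", then "Anticipating a 10% attrition rate, the sample size was adjusted to 75 subjects per group". The inflation checks: 67 / (1 − 0.10) = 74.4, rounded up to 75. The 67 itself reproduces for a two-sample t-test with d = 0.433 when the test is one-sided (power 0.802); a two-sided test needs 85. That is a separate matter and does not enter below.

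**Number of candidates.**
- Base parameters: 5 indicators × 4 muscles × 2 legs = 40 (Primary and secondary objectives; Primary outcome).
- Derived indices, by my count: 4 symmetry indices + 8 activation ranks + 8 contribution rates = 20, giving about 60.
- Cases per candidate: 75/40 = 1.9; 75/60 = 1.25.

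**False positives at the screen.** The 0.05 level is taken as the screening threshold. For m independent null parameters, the chance of at least one is 1 − 0.95^m, and the expected number is 0.05m:
- m = 20: 64%, 1 expected
- m = 40: 87%, 2 expected
- m = 60: 95%, 3 expected

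**Why a survivor must look predictive.** Pearson correlation with a two-level group is the same test as the pooled t-test. With 75 per group the critical t is 1.976 on 148 df, so a parameter passes only if its observed d is at least 1.976 × √(2/75) = 0.323. For normal data this corresponds to an AUC of about Φ(0.323/√2) = Φ(0.228) = 0.59. The screen therefore puts a floor near 0.59 under the apparent AUC, whatever the truth.

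**Null simulation of the whole chain.** There were 1,000 studies per row, 75 per group, with normal data and no parameter related to frailty. Each study used the correlation screen at 0.05, one joint logistic model with age and gender, and parameters kept at 0.05. AUC and the Youden cut-off were taken on the same people, and AUC again on 1,000 new ones. Correlated parameters came in blocks of five. AUCs are means (5th to 95th percentile) among studies that reached the ROC step.

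| Candidates | Correlation | Noise reaches ROC step | Best single AUC | Combined AUC of survivors | Combined ≥ 0.70 |
|---|---|---|---|---|---|
| 20 | 0 | 59% | 0.614 (0.586–0.648) | 0.629 (0.586–0.694) | 2.9% |
| 40 | 0 | 81% | 0.619 (0.590–0.659) | 0.649 (0.592–0.725) | 14.2% |
| 60 | 0 | 92% | 0.623 (0.593–0.658) | 0.666 (0.594–0.752) | 25.5% |
| 40 | 0.5 | 63% | 0.615 (0.587–0.656) | 0.633 (0.587–0.699) | 4.8% |
| 40 | 0.8 | 35% | 0.607 (0.582–0.645) | 0.615 (0.582–0.673) | 2.0% |
| 60 | 0.5 | 77% | 0.618 (0.588–0.656) | 0.643 (0.588–0.717) | 10.0% |

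In every row the mean AUC in new people was 0.50. The Youden cut-off showed sensitivity of about 0.60 and specificity of about 0.63. A single-parameter AUC of 0.70 or more occurred in at most 0.3% of these studies.

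**Sensitivity checks.**
- With 67 per group (40 and 60 independent candidates), the best single AUC was about 0.63 and the combined AUC 0.66 to 0.67.
- The protocol speaks of models in the plural. With a separate adjusted model per parameter (400 studies per scenario), noise reached the ROC step in 91% (60 candidates, correlation 0.5), 78% (60, 0.8) and 65% (40, 0.8) of studies, against 77%, 47% and 38% with a joint model in these scenarios.
- With 60 candidates and within-muscle correlations of 0.95 (amplitude) and 0.9 (frequency), age and gender omitted, the best single AUC was 0.61 and the combined AUC 0.63.

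**The case against.** Several stronger readings are tempting, and the documents do not carry them.

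- **That noise would reliably yield a useful AUC.** It would not. Under a joint model between 8% and 65% of null studies send nothing to the ROC step. When something gets through, an AUC near 0.61 with sensitivity and specificity near 0.6 is weak.
- **That 0.67 is the typical inflated value.** A model holding every screened parameter does reach a median of 0.67 in a null simulation (60 correlated candidates, 67 per group). But the protocol sends only parameters significant in the logistic step to ROC. The single-parameter 0.61 to 0.62 matches that step most directly, and 0.67 is the top of the range for survivors combined.
- **That the ROC certainly contrasts extremes.** The scoring says "a score of 0 indicates no frailty" and places 1 to 2 as pre-frailty, so score-0 controls are the likely reading. Yet controls are described only as without frailty or non-frail, which could admit scores of 1 to 2. The documents do not settle it.
- **That the correlation step is itself an error.** For normal data it repeats the planned t-test. That is redundant, not wrong.

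It can also be said that validation details may sit in a full protocol or analysis plan not shown, and that the Abstract says only that predictive capability will be explored. Both are fair and limit the weight of the point. They do not remove it: the article itself states the selection rule, and followed as written that rule produces biased accuracy figures for a named secondary objective.

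**Conclusion.** The concern holds as a bias of moderate size. Selection, refitting and cut-off choice on the same 150 people will make AUC, sensitivity, specificity and cut-offs optimistic. With no true signal and one joint model, a noise parameter reaches the ROC step in roughly 35% to 92% of studies, and more often with separate models. Its apparent AUC is then about 0.11 to 0.12 too high for the best single parameter, and 0.12 to 0.17 too high for survivors combined. This matters most for modest findings: an observed AUC of 0.60 to 0.67 could not be told from noise by this procedure. A single-parameter AUC of 0.70 or more would be hard to explain by selection alone.

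The size rests on assumptions that the article does not fix: 20 to 60 candidates, correlation of 0 to 0.8 within blocks, normal data, the 0.05 level at both selection steps, and no modelling of the matching. The direction of the bias does not depend on them. The point should be acted on, but it does not touch the primary group comparison.

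**What to change.** - Repeat the entire procedure (screen, logistic selection, cut-off search) inside each bootstrap resample or each fold of a repeated cross-validation. Report optimism-corrected AUC, sensitivity and specificity with intervals.
- Label all cut-offs exploratory until validated in an external sample.
- Preferably start from a short pre-specified list of non-redundant parameters, since RMS, IEMG and AEMG are amplitude measures of the same signal. Penalised regression is an option, not a requirement; resampling the stated procedure also corrects the optimism.
- State whether controls must have a Fried score of 0. If so, describe the result as discrimination of frail from score-0 adults, not as screening or early-detection accuracy.

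The cost is some extra programming, possibly outside SPSS 24.0, and a lower reported AUC. No new data or participants are needed.

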### Quality control

In the present study, comprehensive quality control measures will be implemented to ensure that every stage from participant recruitment to data analysis is performed in strict accordance with standard operating procedures. All potential subjects will undergo a detailed screening process and sign an informed consent form prior to participation. Data collection will be carried out by professionally trained and accredited rehabilitation physicians and research assistants to ensure the accuracy and consistency of the questionnaires and related tests. To prevent data entry errors, a dual data entry system will be employed, and data will be regularly checked for completeness and accuracy. Data hypothesis testing will be conducted prior to statistical analysis to ensure that appropriate statistical methods are used and potential confounding variables are considered in the analysis. The study will adhere to strict ethical guidelines to safeguard participant privacy and data security, and participants will be allowed to withdraw from the study at any time. The entire process will be overseen by an independent quality control team to ensure high standards and reliability of the study. These measures will collectively ensure the validity of the study results and provide a solid scientific basis for understanding the characteristics of EMG signals in frail older adults.

## Discussion

Frailty’s impact on older adults’ health has emerged as a focal point of recent research. Frailty is a dynamic, reversible geriatric syndrome that exists between independence and the need for care. Effective preventive interventions can significantly mitigate its onset and progression [28]. As the population ages, researchers have conducted extensive studies on the measurement of frailty, exploration of its pathogenesis, and the development of management strategies [29]. Despite these efforts, research into the pathogenesis of frailty remains less developed compared to other areas. Notably, no studies have specifically examined the surface electromyography characteristics of the lower extremities in frail older adults. Globally, there is no established gold standard for screening frailty, yet walking speed—a component of the Fried phenotype and the most extensively studied single frailty assessment [24]—has proven to be a crucial independent predictor of adverse clinical outcomes and patient-reported results [30,31]. Walking involves complex systemic mechanisms, and the specifics of its slowdown are not fully understood; however, lower limb biomechanics represent one of the key elements. Moreover, the application of surface electromyography has recently extended beyond traditional fields into areas such as obstetrics, preventive medicine, aging research, and robotics, covering applications in gait and posture analysis, biofeedback, motor synergy, and modeling [19,32]. Thus, exploring the surface EMG characteristics of frail older adults’ lower limbs holds significant clinical importance and could (1) provide sensitive screening indicators for the early detection and prevention of frailty, enabling timely medical intervention and optimization of treatment strategies, (2) offer new insights into the complex mechanisms of age-related frailty, enhancing our biological understanding of this condition, and (3) serve as a scientific basis for assessing lower limb muscle function and developing rehabilitation programs, thereby improving the quality of life for older adults.

Some limitations of this study should be acknowledged. Firstly, as a case-control study, it will not include follow-ups to determine if non-frail older adults who later develop frailty will have surface EMG parameters similar to those observed in the frail older adults; this makes it impossible to definitively establish a causal relationship between changes in surface EMG parameters and frailty. Therefore, we plan to conduct follow-up studies to track the progression of these participants. Secondly, due to financial and time constraints, this study will not be a large-scale multicenter study nor will it analyze a wide range of muscle groups. However, the analysis will strictly adhere to established protocols to ensure as much precision as possible. We aim to include more comprehensive muscle group analyses in future studies.
